#### Cognitive device system

The VRSS Home Tablet, developed by Khymeia Ltd. [38], is a Class I medical device that holds a CE marking, signifying compliance with European Union regulations for medical devices. This designation underscores the device’s safety and effectiveness in addressing specific medical conditions. The centerpiece of the VRSS is its Cognitive Module, which is meticulously designed to target neurological pathologies associated with cognitive functions. This module encompasses a range of activities meticulously curated to stimulate and rehabilitate cognitive processes. By leveraging the Virtual Reality (VR) potential, the VRRS provides a non-immersive experience, ensuring accessibility and comfort for users. This technology can be seamlessly integrated into a home-based rehabilitation program, allowing individuals to engage in tailored exercises from their own environment.

#### Patient allocation in groups

During the *intervention phase*, enrolled patients will be randomized and allocated into three groups (1:1:1 allocation ratio, see the paragraph “Participants randomization” and Fig 1), each undergoing related interventions of equal daily, weekly, and overall training duration (90 minutes total per day, 5 days per week, for a total of 8 weeks).

Group 1—*Motor Training Alone*: Participants will engage in motor training, encompassing a 20-minute walking session, along with balance exercises, postural control exercises, proprioceptive exercises, joint mobilization exercises, and muscle strengthening exercises, collectively spanning 25 minutes. Subsequently, a 45-minute muscle relaxation session will follow, in order to reach the established 90 minute overall duration.Group 2—*Paper-Pencil Cognitive Intervention combined with motor training*: Participants will undertake motor training, mirroring Group 1 (45 minutes), supplemented by a standard cognitive intervention. This cognitive intervention involves executing paper-pencil exercises targeting attention, memory, executive function, visuo-spatial abilities, and space-time orientation (45 minutes total for the entire battery of paper-pencil exercises).Group 3—*Digital Cognitive Intervention combined with motor training*: Participants will perform motor training akin to Group 1 (45 minutes), in combination with a digital cognitive intervention (45 minutes total for the entire battery of digital exercises). This intervention comprises interactive cognitive exercises focused on attention, memory, executive functions, visual-spatial ability, and space-time orientation. The exercises will be facilitated by specific software and hardware (VRRS Home Tablet, Khymeia Srl).

### Outcome measures

#### Primary outcome measure

The primary measure implemented for the present study will be the MMSE (normed total) [39].

#### Secondary outcome measures

The assessment process will encompass various domains, including motor performance, functional performance, cognitive performance, health-related quality of life (HR-QoL), and psychological variables (mood and psychiatric assessment), caregiver burden, adherence, and health care communication and system usability (when the digital device was utilized). Regarding motor performance, we will administer the 6-minute walking test (6MWT) [40] and the Time Up and Go (TUG) test [41]. In terms of functional assessment, we will employ both the Basic Activities of Daily Living (BADL) [42] and the Instrumental Activities of Daily Living (IADL) [43]. In the cognitive domain, patients will primarily undergo the Trail Making Test (TMT-A) [44]. For psychological variables and quality of life, we will administer the following battery of assessments: Generalized Anxiety Disorder 7-Item Scale (GAD-7) [45], Patient Health Questionnaire-9 (PHQ-9) [46], and European Quality of Life (EuroQoL) [47]. Caregivers will complete the Family Strain Questionnaire (FSQ) [48],the Neuropsychiatric Inventory (NPI) [49], and a guided interview to support patients’ observation during daily exercises. In terms of adherence and communication related to health care management, patients will participate in a phone interview to assess program adherence (see Table 1) and complete the Communication Assessment Tool (CAT) [50]. Lastly, to evaluate the usability of the digital system utilized, we will administer the System Usability Scale (SUS) (Group 3, Digital Cognitive Intervention only) [51].

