**System Usability Scale (SUS)** [51]	System usability	Patient-perceived usability	Self-reported assessment of the degree of perceived usability as a result of using a wide variety of devices and systems. The total scores are between 0 and 100, the higher the scores, the higher the degree of perceived usability. The score ranges from A = excellent usability to F = poor usability, based on the normal distribution of the percentile range of mean scores.

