#### Intervention phase

The intervention phase itself will be conducted by the collaborative effort of the Neurophysiopathology, Psychology, and Neurorehabilitation Department at ICS Maugeri, spanning across Montescano (PV) and Pavia, Italy. Outcome measures will be administered at the Neurophysiopathology and Psychology Departments of ICS Maugeri in Montescano and Pavia (see Table 1).

After the assessment, patients willing to participate will be asked to sign a written informed consent in order to join the study. Consequently, participants will be randomly assigned to one of the three intervention groups (see the paragraph “Participants randomization” and Fig 1).

For motor rehabilitation, patients will be given precise instructions on the prescribed exercises by a physiotherapist during the first week at ICS Maugeri. In this initial week, the first session for each exercise will be supervised (pre-training). The pre-training is considered part of the intervention training. After this, patients will continue with the exercise routine independently on a weekly basis (see Table 2 for details).

**Table 2 pone.0306256.t002:** Weekly schedule per trial group.

		*Duration*	Day 1	Day 2	Day 3	Day 4	Day 5
			*Domain (s)*				
**Group 1** (90 min)	*Motor functions*	20 minutes	Fast-paced walking	Fast-paced walking	Fast-paced walking	Fast-paced walking	Fast-paced walking
		25 minutes	Balance and coordination	Postural control	Joint mobilization	Proprioception	Balance and coordination
		45 minutes	Muscle relaxation	Muscle relaxation	Muscle relaxation	Muscle relaxation	Muscle relaxation
**Group 2, Group 3** (90 min)	*Motor functions*	20 minutes	Fast-paced walking	Fast-paced walking	Fast-paced walking	Fast-paced walking	Fast-paced walking
		25 minutes	Balance and coordination	Postural control	Joint mobilization	Proprioception	Balance and coordination
	*Cognitive functions (paper-pencil or Khymeia VRSS Evo)*	45 minutes per day	Orientation Memory Attention/executive functions Visual-spatial functions	Memory Attention/executive functions Visual-spatial functions	Orientation Memory Attention/executive functions Visual-spatial functions	Memory Attention/executive functions Visual-spatial functions	Memory Attention/executive functions Visual-spatial functions

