As for *cognitive rehabilitation* (including both paper-pencil and digital exercises), a process similar to that of motor exercises will be followed. In the initial weekly session, a psychologist will provide supervision. Following this, patients will undertake the exercise program on a weekly basis, adhering to a designated daily schedule of activities (Table 2).

Paper-pencil exercises will be curated by a neuropsychologist from a pool of options, carefully chosen in alignment with well-established neuropsychology standards [36,37].

Digital-based exercises will employ the Khymeia Virtual Reality Rehabilitation System (VRSS) Home Tablet [38] (see below). More in detail, the paper-pencil exercises are selected matching those offered by the Khymeia VRSS system, aiming to minimize uncontrollable biases and assess the effectiveness associated with different modes of exercise administration, while maintaining consistency in the exercise type/nature.

Participants across all three groups will undertake training sessions independently within their homes. The adherence to the training program will be assessed weekly through remote verification by both the physiotherapist and the psychologist. This will involve a semi-structured qualitative interview (see Table 1). Caregivers will play an observational role in the intervention, and they will be provided with comprehensive and standardized training sessions. The training will cover: recognizing and avoiding common biases, detailed instructions on how to observe and report behaviors and outcomes as well as techniques for maintaining consistency in observation and reporting. Furthermore, caregivers will be interviewed weekly to discuss patient adherence and any encountered challenge (Table 1).

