#### Participants randomization

This will be a randomized parallel group trial with a 1:1:1 allocation ratio. Randomization will be performed using a block randomization algorithm (block size of 15) based on Matlab random number generator (MATLAB version: R2014a, Natick, Massachusetts: The MathWorks Inc) to ensure quantitative symmetry of patients assigned to the three groups even during enrolment and to allow for balanced interim analyses. Randomization will be centralized and performed by an independent biostatistician not involved in the trial, from the Biomedical Engineering Unit. Each patient will be given a unique patient number and a randomization code for the allocation at enrolment, so that the staff enrolling participants will know which treatment each patient will be assigned to only once the patient has been enrolled [55]. Finally, the biostatistician responsible for generating the randomization list and the biostatistician responsible for analyzing the data will be unaware of the association between randomization codes and treatment group. Furthermore, to ensure examiner blinding to the study condition, group allocation will be also concealed using alphanumeric codes assigned by a project manager after randomization. Group anonymization will minimize bias in the administration of study measures.

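### Examiner blinding is asserted, but coded group labels alone do not secure it for the examiner-administered MMSE

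*Protocol article*

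**What the plan says.** Participants randomization (Protocol article) makes the claim and gives the mechanism: "to ensure examiner blinding to the study condition, group allocation will be also concealed using alphanumeric codes assigned by a project manager after randomization". It adds that this anonymization will reduce bias when the measures are given. The same section says that enrolling staff learn a patient's treatment once the patient is enrolled.

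Other sections bear on whether the code is enough:

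- **Delivery.** Intervention phase: "The intervention phase itself will be conducted by the collaborative effort of the Neurophysiopathology, Psychology, and Neurorehabilitation Department at ICS Maugeri".
- **Testing.** Same section: "Outcome measures will be administered at the Neurophysiopathology and Psychology Departments of ICS Maugeri in Montescano and Pavia".
- **Training.** For the cognitive exercises, which only Groups 2 and 3 receive: "In the initial weekly session, a psychologist will provide supervision".
- **Adherence.** Same section: "adherence to the training program will be assessed weekly through remote verification by both the physiotherapist and the psychologist".
- **Enrolment.** Study timeline has the Neurophysiopathology and Psychology Units carry out participant selection at T0.
- **Arm-specific instrument.** Secondary outcome measures: "we will administer the System Usability Scale (SUS) (Group 3, Digital Cognitive Intervention only". Table 1 describes this scale as "Self-reported assessment of the degree of perceived usability as a result of using a wide variety of devices and systems".

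The primary outcome is the MMSE normed total (Primary outcome measure). Outcome measures are given at T1, after 8 weeks of training, and at T2, 3 months after training ends.

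**The concern.** Each patient knows whether the daily programme is motor exercise with relaxation, paper exercises or tablet exercises, so patients cannot be blinded. An examiner gives and scores the MMSE. Blinding of that examiner is therefore the main protection of the primary outcome against detection bias.

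Coded labels protect someone who reads a list or a dataset. They do nothing about what an examiner knows from contact with the patient. An examiner who also enrolled, trained or telephoned the patient, or who gives out or collects a questionnaire that only one arm receives, knows the arm whatever the code says. If that knowledge shifts scoring or prompting in one arm, the shift is indistinguishable from a treatment effect.

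**Working it through.** **1. Routes by which an examiner could learn the arm**

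| Route | Where in the article | What it reveals | Closed by a coded label? |
|---|---|---|---|
| Enrolling the patient | Participants randomization; Study timeline | Any arm | No |
| Supervising cognitive training | Intervention phase | Group 2 or 3 | No |
| Weekly adherence checks | Intervention phase; Table 1 | Any arm, from talk about the exercises | No |
| Handling the SUS | Secondary outcome measures | Group 3 | No |
| Patient or caregiver mentions the training | Follows from the open home programme | Any arm | No |

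In each of the first four rows the route is open only if the MMSE examiner is the person in that role. The article neither says so nor rules it out.

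**2. Reproducing the plan's own figure**

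Inputs from Sample size: group means 0, 0.7 and 1.4; SD 1.41; alpha 0.05; power 0.80; one-way ANOVA.

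- Noncentrality λ = n·Σ(mean − grand mean)²/SD², with Σ = 0.7² + 0 + 0.7² = 0.98.
- n = 20: λ = 20·0.98/1.9881 = 9.86, power 0.787.
- n = 21: λ = 21·0.98/1.9881 = 10.35, power 0.809.

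So 21 per group (63) is reproduced, and 63/(1 − 0.16) = 75 is also reproduced. These figures neither support nor weaken the blinding point. They fix n and SD for the next step.

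**3. Scale of the risk under assumed bias**

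Assume no true effect and a spurious mean shift b in one arm of 21. The values of b are assumptions. So is the SD of 3, shown as a less favourable alternative to 1.41.

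*Overall ANOVA.* With one of three means shifted, Σ = (2/3)b², so λ = 21·(2/3)·b²/SD² = 14b²/SD². The 5% critical value of F on 2 and 60 degrees of freedom is 3.15.

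*Tukey pairwise, shifted arm against one other.* SE = SD·√(2/21), which is 0.435 at SD 1.41. The critical |t| is 3.399/√2 = 2.403. The noncentrality is b/SE.

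| b (points) | λ, SD 1.41 | ANOVA rejects | b/SE | Tukey rejects | λ, SD 3 | ANOVA rejects, SD 3 |
|---|---|---|---|---|---|---|
| 0 | 0 | 5% | 0 | 1.9% | 0 | 5% |
| 0.25 | 0.44 | 8.3% | 0.57 | 4.0% | 0.10 | 5.7% |
| 0.5 | 1.76 | 19.5% | 1.15 | 11.2% | 0.39 | 7.9% |
| 0.7 | 3.45 | 34.8% | 1.61 | 22.2% | 0.76 | 10.9% |

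The plan makes Tukey comparisons only after a significant ANOVA. A simulation with that condition at SD 1.41 gives about 3.7%, 10.7% and 21.4%, so the picture is unchanged.

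**The case against.** A reader might infer that examiner blinding fails in this trial. The documents do not support that, for these reasons:

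- **Departments, not persons.** No sentence says that the MMSE examiner enrols, trains or telephones patients. Separate staff within one department would fit the text.
- **The SUS is weaker ground than it looks.** Table 1 calls it self-reported, and nobody is named as handling it. It can reveal only Group 3.
- **SUS timing is not established.** The assessment schedule is in Fig 1, which is not available here. The timeline's general reference to outcome measures cannot be read as applying to every entry in Table 1, because that list includes weekly and daily interviews.
- **Carry-over from T1 to T2 misses the powered comparison.** Sample size defines efficacy as the change from enrolment to end of treatment. Knowledge gained from an SUS given after the MMSE at T1 could affect only T2, and so the repeated-measures ANOVA but not the T1 change.
- **Direction is not settled.** Study end-point expects the digital arm to do best, but the Discussion leaves digital against paper open. The training psychologist would know Groups 2 and 3 alike. A bias specifically in favour of Group 3 does not follow.
- **The MMSE is structured**, and the limitations section says staff familiarity keeps variation in its administration low.

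All of this stands, and it limits the conclusion. It could also be said that an assessor rota and the order of tests are details for the full protocol. That would answer a complaint about silence. Here the article names a specific mechanism, says it ensures examiner blinding, and elsewhere describes procedures that the mechanism cannot cover.

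**Conclusion.** The point holds in limited form: the stated mechanism does not secure the stated property. Whether any examiner would in fact learn the arm cannot be told from the article. The firmer grounds are the enrolment, training and adherence roles. The SUS is an additional, weaker route.

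The size depends wholly on assumptions. For a spurious shift of 0.25 to 0.7 points in one arm, set against the 1.4-point target difference, the overall ANOVA's false-positive rate would be about 8% to 35% at SD 1.41 and about 6% to 11% at SD 3. A Tukey pairwise comparison at SD 1.41 would reject about 4% to 22% of the time against about 2%. The documents give no estimate of such a shift, and the calculation applies it as a mean over the whole arm, so these rates show scale and are not a forecast.

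**What to change.** Amend Participants randomization, with a cross-reference in Secondary outcome measures, to state that:

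1. At T1 and T2 the MMSE and TMT-A are done before any instrument that reveals the arm.
2. The SUS is self-completed afterwards, collected by someone other than the MMSE examiner, and withheld from that examiner until the patient's T2 visit is complete.
3. Patients and caregivers are asked not to mention their training to the examiner.
4. The MMSE examiner, drawn from existing staff, is someone who did not enrol, train or telephone that patient.

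The weekly adherence calls can stay as planned, provided their content is kept from the examiner. The Communication Assessment Tool need not move, because it is not specific to an arm.

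Items 1 to 3 need only wording and ordering. Item 4 needs a rota across the two units and two centres. The article gives no staffing numbers, so its feasibility is for the sponsor to confirm. The cost is some scheduling effort. Endpoint, sample size and analysis are unchanged.

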### Materials

See Table 1 for an extensive description of the instruments administered.

### Study timeline

**T0 (Baseline):** The Neurophysiopathology and Psychology Units will collect and assess clinical and diagnostic data available at baseline, together with the inclusion and exclusion criteria, to proceed with the participant selection. Measures required by the study will be therefore administered (See Table 1). Participants will therefore be randomized into three groups (Figs 1 and 2).**T1 (Post-training):** the outcome measures will be administered after 8 weeks of training.**T2 (Follow-up):** the outcome measures will be furtherly administered 3 months after the end of the training.

**Fig 2 pone.0306256.g002:**
[figure not shown]
Study flowchart. GPCog, General Practitioner Assessment of Cognition; CIRS, Cumulative Illness Rating Scale; CDR, Clinical Dementia Rating Scale.

### Study end-point

Effectiveness will be assessed according to the cognitive performances measured by MMSE [39]. As for the difference among groups, a difference (delta) of +1.4 will be hypothesized between the group *Digital-cognitive intervention combined with motor training* and the group *Paper-pencil cognitive intervention combined with motor training*, whereas a delta of +2.8 is expected to be observed between the subgroup *Digital-cognitive intervention combined with motor training* and the group *Motor intervention alone* [52].

### Data analysis

#### Sample size

The sample size was calculated considering the MMSE score, the primary outcome of the trial. We required the sample size to be large enough to detect a difference in efficacy (measured as MMSE at the end of treatment—MMSE at enrolment) of 1.4 MMSE points between the most effective treatment and the least effective treatment. This value was selected because it is reported in literature as the lowest threshold for the minimum clinically important difference (MCID) [39,53]. To be conservative, the third treatment was assumed to be as effective as the average of the other two. The aim was to detect this difference with a two-sided type I error of 5% and 80% power. From previous studies in populations similar to ours [54], the standard error of measurement (SEM) for the MMSE is 1 point, giving an SD of 1.41 (resulting in a Cohen’s effect size close to 1). The sample size was then estimated at 63 patients (21 per group). Taking into account the possibility of losing some patients (up to 16% of drop-outs), the required sample size was set at 75 patients (25 per group). Computations were performed using the ’proc power’ of the SAS statistical package with the following parameters: one-way ANOVA as statistical model, 0, 0.7 and 1.4 as group means, 1.41 as standard deviation, 0.05 as alpha and 0.8 as power (SAS/STAT, release 9.4, SA Institute Inc., Cary, NC, USA).

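### The planning SD of 1.41 comes from the MMSE's standard error of measurement and makes no allowance for patients differing in true response, so the stated 80% power for a 1.4-point range is a best case

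*Protocol article*

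**What the plan says.** The Sample size section takes as its target a "difference in efficacy (measured as MMSE at the end of treatment—MMSE at enrolment) of 1.4 MMSE points" between the most and the least effective arm, with the third arm placed midway. The stated goal is "The aim was to detect this difference with a two-sided type I error of 5% and 80% power".

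The only variability input is "the standard error of measurement (SEM) for the MMSE is 1 point, giving an SD of 1.41", attributed to earlier studies in similar populations and described as "resulting in a Cohen’s effect size close to 1". The software inputs are "one-way ANOVA as statistical model" and "0, 0.7 and 1.4 as group means, 1.41 as standard deviation, 0.05 as alpha and 0.8 as power". The result is 21 per group (63 in all), raised to 25 per group (75) for up to 16% drop-out.

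Two other sections bear on the point. Study end-point expects a larger spread: digital plus motor ahead of paper-pencil plus motor by 1.4 points, and ahead of motor alone by 2.8. Statistical analysis brings in ANCOVA only when a baseline comparison turns out significant.

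**The concern.** The error term of a one-way ANOVA on change scores is the spread of observed change among patients in the same arm. Under the usual measurement model that spread has two parts: error in the two MMSE readings, and real differences between patients in how far they moved. The SEM supplies the first part. The sizing paragraph adds nothing for the second and shows no sensitivity range. Its one claim to be conservative concerns where the middle group mean is placed, not the SD.

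The 63 and 75 patients, the 80% power and the standardised effect near 1 all rest on this number. If the SD of change is larger than 1.41, the trial has less than the stated power to detect the smallest difference it regards as clinically important. A reader who relies on the 80% could then give a non-significant result more weight than it deserves.

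**Working it through.** **Inputs (Sample size section).** Group means 0, 0.7 and 1.4; SD 1.41; alpha 0.05; three equal groups; SEM 1 point; drop-out 16%.

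**Where 1.41 comes from.** If two readings carry independent errors with SD equal to the SEM, the error SD of their difference is √2 × 1 = 1.414. The article does not write this out, but it is the evident step from 1 to 1.41.

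**Power formula.** The overall F test has 2 and 3n − 3 degrees of freedom and non-centrality λ = n × Σ(mean − grand mean)² / SD². Here Σ = 0.49 + 0 + 0.49 = 0.98.

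**Reproducing the plan.** With n = 21 and SD 1.41, λ = 21 × 0.98 / 1.9881 = 10.35 on 2 and 60 degrees of freedom, and power is 80.9%. With n = 20 it is 78.7%. So 21 per group is the smallest size that meets the target, and 63 / (1 − 0.16) = 75. The plan's figures are correct for the inputs given.

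**Slack.** Solving for the SD at which power equals 80%:
- 21 per group: SD 1.425. With SEM 1, this leaves room for a true-change SD of √(1.425² − 2) ≈ 0.18 points.
- 25 per group (no drop-out): SD 1.56, which leaves room for √(1.5616² − 2) ≈ 0.66 points.

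**Sensitivity.** If the SEM is error only, SD of change = √(2 × SEM² + SD of true change²). A true-change SD of 1 point gives √(2 + 1) = 1.73. Every SD above 1.41 in the table is an assumption, because the article reports no SD of change. The detectable range is the distance between the extreme means (third mean midway) that gives 80% power. It scales with the SD: 1.4 × SD / 1.4252 at 21 per group and 1.4 × SD / 1.5616 at 25.

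| SD of change | Power, 21 per group | Power, 25 per group | Detectable range, 21 | Detectable range, 25 |
|---|---|---|---|---|
| 1.41 (plan) | 80.9% | 87.8% | 1.39 | 1.26 |
| 1.73 | 62% | 71% | 1.70 | 1.55 |
| 2.0 | 49% | 57% | 1.96 | 1.79 |
| 2.5 | 33% | 39% | 2.46 | 2.24 |
| 3.0 | 24% | 28% | 2.95 | 2.69 |

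**The larger spread in Study end-point.** With means 0, 1.4 and 2.8 and 21 per group, power is 98% at SD 2.0, 90% at SD 2.5 and 76% at SD 3.0. It stays at or above 80% up to an SD of about 2.85.

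**The case against.** Four objections deserve an answer.

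- **The origin of the SEM is not shown.** A reader might infer that 1.41 is pure test-retest error and a strict lower bound. The article does not support that, because it does not say how the cited SEM was obtained. If it was computed as the SD of retest differences divided by √2, multiplying back by √2 returns an observed SD of change over that retest interval, including any true change within it. This stands, and it is why 1.41 is called probably low rather than a proven floor. Neither derivation, though, covers patients responding differently to eight weeks of training.
- **The size of the shortfall is unknown.** A reader might infer that the design will certainly miss its power, or that real power is half the stated figure or less. Halving it at 21 per group needs an SD of change of about 2.25, and nothing in the article fixes that value. This also stands.
- **The authors expect more than 1.4 points.** Under the Study end-point spread the trial would be well powered over most of the SD range above. That should be disclosed. But the 80% is claimed for a 1.4-point range, chosen as the lowest MCID threshold, and a larger hoped-for effect does not justify the SD.
- **The heterogeneity evidence is limited.** The Introduction's description of a highly heterogeneous population concerns the wider patient group. Eligibility here is restricted by CDR, age and time since onset, and home training is checked weekly. Variety in aetiology or severity is not itself variance in 8-week change. So the point should not rest on that description. It rests on the absence of any allowance for differing response.

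**Conclusion.** The point holds as a criticism of a planning assumption and of the power claimed from it. It is not an arithmetic error: the sample size follows correctly from its inputs. The SD is derived from the SEM and makes no provision for variation in true response, so the 80% for a 1.4-point range is a best case with almost no margin. At 21 evaluable per group it is lost once the SD of change passes about 1.43, and with all 75 evaluable once it passes about 1.56. The direction follows from the formula, since any added variance lowers power. How far power falls depends on an SD of change that the article does not give, so the 62% to 24% at 21 per group for SDs of 1.73 to 3.0 illustrates the loss and does not estimate it. ANCOVA could recover some precision, but as planned it depends on a significant baseline difference and cannot be counted on.

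**What to change.** 1. In the sample-size text, state that 1.41 is √2 times the SEM and is a best-case SD of change.
2. Restate power and detectable difference at 21 and 25 per group over a range of SDs of change, for example 1.4 to 3.0. Where the Study end-point spread is also shown, label it as a different scenario from the one the 80% refers to.
3. Make adjustment for baseline MMSE part of the primary analysis in all cases, not conditional on a baseline significance test. The gain in precision cannot be quantified from the article.
4. If the primary comparison is non-significant, report the confidence intervals for the group differences against 1.4 points.

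The cost is a rewritten paragraph, a less favourable power statement and one change to the analysis specification. Baseline MMSE is already collected at T0, so no extra patients, visits or measurements are needed.
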